## Abstract

**Introduction:**

Depression is a major global health challenge, with onset commonly occurring in youth. There is an urgent need to better understand the epidemiology of depression to facilitate better interventions and preventions that are person-specific and time-specific. Long-term depression trajectories and ecological momentary assessment (EMA) can help address this need. Embedding EMA designs within established longitudinal cohorts offers a uniquely powerful approach to examine depression in both long- and short-term settings and to identify distal and proximal modifiable risk factors for depression.

**Methods and analyses:**

Our study will include ~450 participants from the Twins Early Development Study and ~250 participants from the Avon Longitudinal Study of Parents and Children (ALSPAC) who have depression trajectories data previously collected between late childhood and early adulthood. Participants will be recruited from four different depression trajectories in each cohort based on participants’ prior symptoms. They will undertake EMA surveys of depression, sleep, physical activity, substance use, diet, recent activities and social interactions three times a day for 6 weeks, with more detailed questionnaires at baseline, 2, 4 and 6 weeks. We will use descriptive analysis, mixed effects models and dynamic structural equation modelling to examine how depression occurs over this time, how potentially modifiable factors affect depression and vice versa and how these effects vary by different life-course trajectories. This study is designed to identify people at heightened risk of depression and/or identify modifiable targets that could inform more effective prevention and intervention strategies.

**Ethics and dissemination:**

Favourable ethical opinions were given by the Edinburgh Medical School Research Ethics Committee (REC References: 25-EMREC-001 and 25-EMREC-030) and the ALSPAC Law and Ethics Committee (Ref: 0027 B4792). The results will be disseminated through journal publications, conferences and seminar presentations and to relevant stakeholders, such as those with a history of depression, policy makers and clinicians.

STRENGTHS AND LIMITATIONS OF THIS STUDYThis study will combine intensive longitudinal data (ecological momentary assessment [EMA]) with traditional longitidinal data to examine depression in both the long and short term, for the first time.This study has a large sample of 700 participants who will complete complete brief EMAs up to three times a day, for 6 weeks, with additional baseline and fortnightly questionnaires.A range of measures will be used during the EMA study, allowing for the identification of important modifiable factors related to depression in real time, for specific groups of individuals with different depression histories.In Avon Longitudinal Study of Parents and Children, a subset of participants will also wear smartwatches to passively collect data on sleep, activity and heart rate.Attrition is likely to play a role in the EMA data collection, especially for participants with a history of depression.

## Introduction

Depression is a global health challenge, affecting over an estimated 330 million people worldwide,^1^ and predicted to be the leading cause of disability by 2030.^2^ Young people are at particular risk of depression,^3^ with emerging evidence that depression is worsening within this population.^4 5^ Depression during this period is associated with wide-ranging and long-lasting economic, social and physiological consequences.^6–9^ Evidence suggests that 50% of people who have ever had depression had an onset before the age of 25,^10^ and almost 50% of those who develop depression between 18 and 40 will have a subsequent episode.^11^ This makes it crucial to prevent or limit depression during earlier life to mitigate later effects. Understanding what modifiable factors and mechanisms influence the course of depression is therefore of considerable clinical, economic and societal importance. Such research could ultimately help identify people at heightened risk of worsening depression and/or identify modifiable targets that could inform more effective prevention and intervention strategies.

Longitudinal studies that track the same people over time are critical to addressing this line of research. Such studies can estimate depression trajectories across development and highlight how depression develops, persists and remits across the life course, as well as what trajectories are specific for different aetiologies and outcomes.^12–14^ Importantly, they have also identified key risk and protective factors such as sex and pubertal timing,^15 16^ genetic vulnerability,^17 18^ early adversity^7^ and the family environment^19 20^ that likely shape depression over time. While such research is important, these studies typically assess depression at yearly intervals or longer. As such, there is a current paucity for what depression looks like in between these assessments, and how depression and its correlates may fluctuate and drive one another in the short-term, from day-to-day or even moment to moment settings. A greater understanding of more granular short-term manifestation could inform treatment provision and illuminate the perpetuating or proximal mechanisms that drive depression in day-to-day life.

Ecological momentary assessment (EMA) has emerged as a powerful tool for addressing this limitation.^21–23^ EMA designs can collect data multiple times a day while participants go about their daily routines, enabling researchers to examine depression as it unfolds in naturalistic settings and to identify how specific contextual factors can shape mood and vice versa, all in close to real time.^24 25^ EMA designs can be paired with passive data collection (ie, through smartwatches) to provide objective measures of factors such as sleep, exercise or heart rate and their relation to daily mood^26^ in a continuous, non-invasive manner. EMA is particularly well suited to capturing the dynamic, person and context-dependent nature of depression, providing the opportunity to measure short-term depression trajectories over a given period. It can also capture symptom variability, the occurrence of correlated factors and perhaps most importantly, reactivity to daily stressors and life events in a way that retrospective designs cannot reliably detect. A growing body of EMA research has demonstrated that short-term fluctuations in depression are both clinically meaningful and informative.^27^ For example, EMA designs have shown that depression is not stable, even across a single day.^28^ Furthermore, momentary factors such as disrupted sleep,^28 29^ reduced physical activity^28 30 31^ and worse social interactions are believed to influence depressive states in the short term.^24 32 33^ However, existing EMA studies of depression have predominantly been conducted in small samples (often clinical populations or student cohorts), without access to broader phenotypic or prospectively ascertained life-course data. This limits their capacity to examine how short-term depressive dynamics fit within the broader context of development and the life course.

To date, long-term trajectory research and short-term intensive data collection have not been conducted in depression research, with only a handful of studies embedding broader EMA designs into longitudinal studies, such as in ADHD research.^34^ This represents a significant missed opportunity to combine detailed data on depression in the moment and short-term depression trajectories, alongside detailed longer-term depression trajectories derived from routinely collected data. Short-term depression symptoms and the modifiable factors that drive them such as sleep, exercise, diet, substance use and social interactions could illuminate proximal mechanisms that underpin longer-term depression trajectories—thus highlighting opportunities for more tailored and targeted interventions and preventions that are time-specific and person-specific. Embedding EMA within established longitudinal cohorts, whose participants have well-characterised life-course depression trajectories, offers a uniquely powerful approach to address this gap. By selecting participants based on previously characterised depression trajectories, it is possible to examine the real-time epidemiology of depression and how it varies across individuals with different histories of depressive experience. This can also be combined with data collected across development, such as psychosocial factors, family history and genetic risk, to identify the momentary risk and protective factors that are most relevant within different trajectories.

In this study, we will use an EMA design embedded within two established longitudinal studies: the Twins Early Development Study (TEDS) and the Avon Longitudinal Study of Parents and Children (ALSPAC) to study depression in both the long- and short-term. Both studies have extensive life-course data on depression and its determinants, allowing us to derive clinically meaningful and robust depression trajectories from childhood to early/emerging adulthood. The nature of this study will allow us to examine how short-term depressive dynamics occur and vary within the context of longer-term depression trajectories and how momentary risk and protective factors, such as sleep, physical activity, diet, substance use, social interactions and stress, contribute to these fluctuations in real time. Furthermore, in a subsample of ALSPAC participants, concurrent passive data collection will be collected via wearable smartwatch devices to enrich this picture by providing objective physiological measures of sleep, physical activity and heart rate, complementing and contextualising the self-reported EMA data.^35 36^ Our core research questions are:

(RQ1) How does depression occur and vary in the short-term—from day-to-day or even moment-to-moment settings in people with different prior life-course depression trajectories?(RQ2) Which momentary risk and protective factors such as sleep, stress, physical activity, diet, substance use and social interactions are most strongly associated with short-term fluctuations and symptoms in depression in daily life, and how do these vary by different depression trajectories?(RQ3) How do short-term depression dynamics relate to longer-term depression trajectories previously characterised in the cohort, and do they mediate or moderate the associations between established risk factors and longer-term outcomes?

Exploratory analyses may be used to address a range of additional questions, including examination of individual differences in the links between momentary risk factors and depression, using machine learning to predict greater levels of depression and to identify further potential targets for personalised and timely intervention. For more ambitious questions like RQ3, we will pre-register analysis on the open science framework.

## Methods and analysis

### Existing study participants

Participants will be drawn from two existing longitudinal cohort studies: TEDS and the ALSPAC. In TEDS, the original sample comprised 13 759 families with newborn twins, who participated in the first assessment wave at 18 months. Families were recruited from the Office of National Statistics’ national register of twins born in England and Wales between 1994 and 1996.^37^ In ALSPAC, pregnant women residing in Avon, UK with expected delivery between 1 April 1991 and 31 December 1992 were invited to take part in the study. A total of 14 901 children alive at 1 year of age participated in ALSPAC.^38–40^ Further cohort information is provided in the online supplemental materials. Overall ethical approval for TEDS was granted by the King’s College London Research Ethics Committee (References: PNM/09/10–104, HR/DP-20/2122060, and RESCM-24/25-22060), and consent was given by participants at each wave. In ALSPAC, overall ethical approval for the study was obtained from the ALSPAC Ethics and Law Committee and the Local Research Ethics Committees. Informed consent for the use of existing data collected was obtained from participants following the recommendations of the ALSPAC Ethics and Law Committee at the time. Participants can contact the study team at any time to retrospectively withdraw consent for their data to be used. Study participation is voluntary and during all data collection sweeps, information was provided on the intended use of data. In TEDS, the study website contains details of all data that is available: https://datadictionary.teds.ac.uk/home.htm. In ALSPAC, the study website contains details of all data that is available through a fully searchable data dictionary and variable search tool and reference the following webpage: http://www.bristol.ac.uk/alspac/researchers/our-data/.

10.1136/bmjopen-2026-122195.supp1Supplementary data

### EMA participants

The present study will include ~450 participants from TEDS and ~250 participants from ALSPAC who have depression trajectories data previously collected between late childhood and early adulthood. We will only recruit participants who have responded to the most recent questionnaire on depression within each study (both assessed in 2025) to ensure that participants belong to the most up to date depression trajectories. Participants in the EMA study will have a mean age of 29.5 years in TEDS and 32.6 years in ALSPAC. All participants will be required to have completed a minimum of two depression assessments (one in childhood/adolescence and another in late adolescence/early adulthood) to be included in the initial trajectory analysis in which to recruit from. Based on recent questionnaire data collected in both cohorts, we have a maximum sample of 3275 participants in TEDS and 3866 participants in ALSPAC from which to recruit participants into the EMA section of the study. Based on previous research,^7 41^ we estimated four similar trajectories per cohort (a stable low trajectory, an adolescent-onset trajectory, an adolescent-limited trajectory and a persistent trajectory), see figure 1. We will recruit equally from each trajectory group to ensure a matched case-control analysis, randomising the order in which we invite participants to join the EMA study. In ALSPAC, ~100 participants will be given Withings smartwatches to passively collect data on sleep, activity and heart rate throughout the study. Figure 2 shows a graphical representation of our study.

**Figure 1 F1:**
[figure not shown]
Depression trajectories in each cohort. N (and percentage of total sample) are given for each trajectory. ALSPAC, Avon Longitudinal Study of Parents and Children; SMFQ, Short Mood and Feelings Questionnaire; TEDS, Twins Early Development Study.

**Figure 2 F2:**
[figure not shown]
Summary of the mood in the moment study design with schematic depression trajectories. Co90s, children of the 90s; EMA, ecological momentary assessment; TEDS, Twins Early Development Study.

### Inclusion criteria

The inclusion criteria for this study require participants to be active and consenting participants of the TEDS and ALSPAC studies and have previously measured data on depression (ie, a minimum of two depression assessments (one in childhood/adolescence and another in late adolescence/early adulthood)) and have completed the most recent questionnaire on mental health. Eligible participants will be invited to join the study if they meet these criteria and will be invited by the TEDS and ALSPAC teams directly through existing contact information held by the studies. In TEDS, only participants who have consented to be contacted about future substudies will be invited to take part. Participants will be required to have a sufficient understanding of written and spoken English language to understand study information and instructions, provide informed consent and participate in the text-based EMA surveys to be completed via smartphone application. Participants will also be required to own a smartphone device with access to either the app store (Apple iPhones) or Google Play Store (Android phones) to download the smartphone application m-Path to allow participation in the study for a period of six consecutive weeks. In ALSPAC, participants must be willing and able to download the Withings smartwatch application and wear a Withings smartwatch for a period of 6 weeks (if consented to this aspect of the study). Across both studies, participants must be available to participate in the study for a consecutive 6 week period without significant breaks while the data collection is live.

### Patient and public involvement

Individuals with and without depression have contributed to the design of this study. We first consulted people with lived experience of depression as part of an ongoing user-led citizen science project called ‘The Depression Detectives’. In their capacity as advisors, they saw value in identifying patterns of depression early through smartphones and to identify key factors that could prevent depression from getting worse and leading to long-term problems. Next, a group of adolescents recruited as part of a patient and public lived experience group determined feasibility of the study, recommending the types of factors to include and duration of the study. Finally, active participants from the ALSPAC study provided guidance on the duration of the study, measures used and amount of reimbursement that would be suitable for the study.

### Data collection

Data collection began in September 2025 and is expected to complete by August 2026. Analysis will be staggered across this period to avoid seasonality effects. Figure 2 shows a graphical representation of our study, where participants will be recruited based on their existing depression trajectories. Participants will then be invited to join this EMA study and provide consent as described above.

Participants who give consent and begin the study will be sent instructions on how to download the ‘M-Path’ EMA smartphone application. In ALSPAC, ~100 random (equal across trajectories) participants will be recruited into the smartwatch element of the study will also be sent instructions on how to download the ‘Withings’ smartphone application. Each participant will be sent their own unique and pseudo-anonymised login that only the respective study teams can use to identify participants.

Participants who successfully join the study will first complete a baseline questionnaire and have 7 days to complete this before they are removed from the study. Completion of this baseline questionnaire will initiate EMA surveys starting the next morning. EMA surveys will occur three times a day (randomly in the morning (08:00 to 09:00), afternoon (13:00 to 14:00) and evening (18:00 to 19:00)) for 6 weeks (for a maximum of 126 surveys), all through the ‘M-Path’ smartphone application. These EMA surveys are designed to be completed in under 3 min, and each daily survey is available for 3 hours from the initial prompt. Reminders were sent after 60 and 120 min. Slightly longer questionnaires (taking ~5 min to complete) are also available to complete at the 2-week and 4-week intervals. A final end-of-study questionnaire is then available to complete at the end of the study at week 6. Participants will be reimbursed £1 for every EMA survey they complete, and £2 for each questionnaire they complete (baseline, 2 week, 4 week and end of study questionnaires). We have also implemented a bonus structure for the EMA surveys. If participants complete 50% of the EMA surveys (63 surveys), they will receive a further £5. Completing 60%, 70%, 80%, 90% or 100% results in a further £10, £15, £20, £25 or £30 bonus, respectively. Therefore, a participant completing 50% of the EMA surveys and two longer questionnaires would be reimbursed £72 (£63 for the 63 EMA surveys, the £5 bonus for 50% completed EMA surveys and £4 for the two longer questionnaires). A participant completing 100% of the EMA surveys and all four longer questionnaires would be reimbursed the maximum £164 (£126 for the 126 EMA surveys, the £30 bonus for 100% completed EMA surveys and £8 for the two longer questionnaires). ALSPAC participants with the smartwatches will receive an additional £10 reimbursement for taking part in smartwatch component of the study. Reimbursement will be given in the form of Love2Shop vouchers, administered by the respective study teams.

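### Staggering the analysis cannot avoid seasonality; staggered recruitment would only spread season across people, leaving a possible, modest confounding of trajectory comparisons

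*Protocol article*

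**What the plan says.** The Data collection section gives the period, "Data collection began in September 2025 and is expected to complete by August 2026", and follows it with the safeguard: "Analysis will be staggered across this period to avoid seasonality effects".

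Three other statements decide what that safeguard can do:

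- **Length of observation.** Under Inclusion criteria, "participants must be available to participate in the study for a consecutive 6 week period without significant breaks while the data collection is live".
- **Start date.** Under Data collection, "Completion of this baseline questionnaire will initiate EMA surveys starting the next morning". A person's place in the calendar is therefore set by invitation, consent and completion of baseline. No assignment to a calendar block is described.
- **Recruitment.** Under EMA participants, "We will recruit equally from each trajectory group to ensure a matched case-control analysis", with the safeguard of "randomising the order in which we invite participants to join the EMA study". The article does not say whether that random order runs across the four trajectories at the same time.

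The Statistical analysis section then plans to relate each person's EMA indices (average level, variability, carry-over from one assessment to the next) to trajectory membership. That is a between-person comparison.

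**The concern.** The article claims a protection that its stated method cannot provide. Staggering an analysis changes when results are computed, not when participants were observed. If the word is a slip for recruitment or data collection, the sentence still promises too much: spreading enrolment over a year distributes season across people but does not remove it from comparisons between people.

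What is at stake is the trajectory comparison in the first research question. Mood, sleep and activity may plausibly vary with time of year. If one trajectory group is observed mainly in autumn and winter while another is observed over the whole period, part of any difference between them would be seasonal. A reader told that seasonality has been avoided would not look for this.

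**Working it through.** **1. What the plan's figures give.** The article states no figure for seasonality, so there is none to reproduce. The block length can be confirmed: 3 surveys × 7 days × 6 weeks = 126, the stated maximum. One block is 42 days, and 42/365 = 11.5% of a year. Nobody is followed across the seasons, so season is almost entirely a between-person variable.

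**2. Can fill speed be derived?** No. With "The present study will include ~450 participants from TEDS and ~250 participants from ALSPAC", equal quotas are 450/4 = 112.5 and 250/4 = 62.5 per trajectory. The pools are given only in total: "we have a maximum sample of 3275 participants in TEDS and 3866 participants in ALSPAC". Sizes per trajectory are in Figure 1, which was not available for this review, and the text gives no uptake rates. The Limitations section says only that people who find the schedule burdensome, or whose depression worsens, may be less likely to join. Differential filling is therefore plausible but not shown.

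**3. Illustration on assumed inputs.**

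- Seasonal effect: A·cos(w(t − 15)), with w = 2π/365 and t in days from 1 January, so the peak is in mid-January. A is in between-person SDs. Shape, peak and A = 0.1 to 0.2 are all assumptions.
- Starts are uniform between day a and day b. The period opens on 1 September (day −122). The last start that allows completion by 31 August is day 242 − 42 = 200.
- Each person's value is the average over their 42 days.

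Averaging over the block and then over start dates gives

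mean = A × k × [sin(w(b + 6)) − sin(w(a + 6))] / [w(b − a)],

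where the 6 is the block midpoint minus the peak (21 − 15), and k = sin(21w)/(21w) = 0.978.

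For the whole period (a = −122, b = 200): [−0.394 − (−0.911)] / 5.543 = 0.0933, and × 0.978 = 0.091A.

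For starts in the first 3 months (91.2 days, b = −30.8): [−0.414 − (−0.911)] / 1.570 = 0.316, and × 0.978 = 0.309A.

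The contrast is 0.309A − 0.091A = 0.218A. The other windows follow in the same way:

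| One group's starts confined to the first | Its mean | Minus whole period (0.091A) | A = 0.1 | A = 0.2 |
|---|---|---|---|---|
| 2 months | 0.091A | 0.00A | 0.00 SD | 0.00 SD |
| 3 months | 0.309A | 0.22A | 0.02 SD | 0.04 SD |
| 4 months | 0.471A | 0.38A | 0.04 SD | 0.08 SD |
| 6 months | 0.567A | 0.48A | 0.05 SD | 0.10 SD |
| 8 months | 0.403A | 0.31A | 0.03 SD | 0.06 SD |

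The zero at 2 months is an accident of the assumed peak date. If all groups share the same distribution of start dates, the expected contrast is zero. The date of analysis appears nowhere in the formula.

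**The case against.** The best reply is that the word analysis is probably a slip, that recruitment over nearly a full year is sound practice, and that randomising the invitation order tends to balance season across trajectories if all four are invited at the same time. Much of this stands. It makes balance at invitation likely under that reading. It does not guarantee balance at enrolment if uptake differs or one quota closes before another, and it does not make the published sentence correct.

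Four stronger readings are tempting, and the documents do not support them:

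- **That season is confounded with trajectory and cohort.** No fill rates or enrolment dates are reported, so this cannot be asserted. No research question is a contrast of TEDS with ALSPAC. With equal quotas in each cohort, different timing between cohorts would not by itself tie trajectory to season.
- **That the bias could be much larger.** If one group started wholly in the first half of the period and the other wholly in the second, the contrast would be 0.568A − (−0.386A) = 0.95A, or 0.10 to 0.19 SD at the same amplitudes. Quota closure does not produce this pattern: both groups begin together and overlap until the faster one closes.
- **That the bias rivals the effects of about 0.2 to 0.3 in the sample size section.** Those are associations between depression and risk factors within each trajectory, not differences between trajectories.
- **That the missing calendar covariate is an omission.** A condensed article may leave covariates to an analysis plan that is not shown.

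**Conclusion.** The sentence is wrong as written and needs correcting. Its stated method cannot deliver the stated property, and the charitable reading delivers a spread of season, not its avoidance.

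Confounding of trajectory with season is possible but not demonstrated. With an assumed mid-January cosine of amplitude 0.1 to 0.2 SD and early closure of one group at 3 to 6 months, the spurious contrast is about 0.02 to 0.10 SD. It is zero under balanced timing and scales directly with the assumed amplitude. Exposure is confined to comparisons between people, chiefly those by trajectory. Associations within a person over six weeks are little affected. This is a modest risk that can be guarded against at very little cost.

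**What to change.** 1. **Replace the sentence**, for example with: *Recruitment will be spread over the data collection period, with remaining invitations released in parallel across trajectories within each cohort, to reduce confounding by season.*
2. **Add sine and cosine terms of calendar date**, or day length, to models that compare people or trajectories.
3. **Report start month by trajectory and cohort**, so that readers can see whether balance was achieved.

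The cost is two degrees of freedom, slightly slower filling of the easier quotas, and a wording change. No new data are needed, since the app-delivered surveys should already carry dates. Two limits apply. Collection began in September 2025, so parallel release can affect only invitations not yet sent. And where groups overlap little in calendar time, the adjustment rests on the assumed seasonal shape rather than on the data.

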### Limitations

There are several limitations of our study that warrant acknowledgement. First, the EMA component captures depressive experience over a period of 6 weeks, providing a relatively brief window into short-term depressive fluctuations and not a continuous record of daily life over months or years. While such a study design is possible, the burden on participants to complete such measures over months or even years is likely to be too great. As such, a key strength remains the ability to link these short-term depressive symptoms with the longitudinal cohort data. Future studies could look to embed regular periodic assessments of EMA into existing longitudinal studies (ie, once every couple of years) to address this.

Second, as with all EMA studies, our present design is likely to be subject to low compliance, participants rapidly completing the surveys and attrition over the study period. Participants who find the EMA schedule burdensome, or who experience significant worsening of depression during the study, may be less likely to complete all assessments or even consent to join the study to begin with, potentially introducing selection bias, as per some previous research.^46–48^ Although our study protocol has been designed to minimise burden with surveys designed to take no more than a few minutes each, and appropriate incentives and support structures will be in place, some degree of non-random attrition is to be expected. Sensitivity analyses will be used to examine the potential impact of missing data on key findings.

Finally, while our study spans two different cohorts and is designed to maximise sample size within our available resources, statistical power for some of the more complex within-person and between-group analyses may be limited, particularly in the subsample completing smartwatches. Power analyses and simulation studies have been used to inform the study design but replication of key findings in independent samples will ultimately be necessary to establish their robustness.

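### The only bias check stated covers missing data, so it does not reach invitees who decline or who are removed at day 7; between-trajectory contrasts in EMA depression level may be biased

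*Protocol article*

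**What the plan says.** Under EMA participants, the protocol article sets the targets: "The present study will include ~450 participants from TEDS and ~250 participants from ALSPAC". The pools are given as a ceiling: "we have a maximum sample of 3275 participants in TEDS and 3866 participants in ALSPAC". Recruitment is described as follows: "We will recruit equally from each trajectory group to ensure a matched case-control analysis, randomising the order in which we invite participants". Eligibility requires a 2025 depression response ("We will only recruit participants who have responded to the most recent questionnaire on depression within each study"). The Inclusion criteria add at least two depression assessments, one of them from childhood or adolescence.

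Under Data collection, those who join "have 7 days to complete this before they are removed from the study". Completing the baseline questionnaire is what triggers the EMA surveys, from the next morning.

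Under Limitations, the article says that people who find the schedule burdensome, or whose depression worsens, "may be less likely to complete all assessments or even consent to join the study to begin with, potentially introducing selection bias". The analytic response that follows is: "Sensitivity analyses will be used to examine the potential impact of missing data on key findings".

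Under Statistical analysis, the short-term depression indices are to be related to trajectory membership, which is the comparison at the centre of RQ1.

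**The concern.** The article names two routes of loss before any EMA data exist: non-consent, and removal for missing the 7-day baseline. It says itself that the first may depend on depression. A missing-data analysis works on records that are incomplete. A person who declined or was removed at day 7 has no EMA record to complete. The threat is stated, but the stated check does not cover it.

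Random invitation order makes the invitees a fair sample of each trajectory. It does nothing about which invitees go on to start, because that selection comes after the invitation.

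At stake is what the enrolled groups represent. The trajectories were defined in the wider cohort. If the people who start are the less unwell members of, say, the persistent group, its EMA depression level is understated. Contrasts with other groups are then biased unless the same shift occurs in those groups.

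**Working it through.** **No figure to reproduce.** The article gives no expected rate of non-participation or day-7 removal, no dependence on symptoms, and no readable scores by trajectory (Figure 1 is not shown). Its 80% power statement concerns associations within a trajectory, which is a different quantity. The sizes below are therefore illustrations.

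**Who each check reaches**

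| Group | Trajectory and 2025 score held | EMA record | Reached by a missing-data analysis |
|---|---|---|---|
| Invited, declined | yes | none | no |
| Joined, removed at day 7 | yes | none | no |
| Started EMA, incomplete | yes | partial | yes |

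**Target as a share of the pool.** TEDS: 450/3275 = 13.7%. ALSPAC: 250/3866 = 6.5%. These are not uptake rates. The pools are maxima, TEDS invitations go only to people who agreed to sub-study contact, and the targets apply per trajectory. They show only that the targets could be met at low uptake.

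**Illustration: assumed inputs**
- 2025 SMFQ scores are normal, truncated to 0-26 (13 items, assumed scored 0-2).
- Probability of starting: logit(p) = logit(u) + ln(OR) × (score − group mean).
- Base uptake u is 15% or 50%. OR per SMFQ point is 0.95 or 0.90.
- Mean among starters = Σ(score × p)/Σp over the group's distribution.

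Means and SDs in the table are before truncation; the contrasts are after it.

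| Persistent (mean, SD) | Low (mean, SD) | u | Full contrast | Contrast among starters, OR 0.95 / 0.90 | Shrinkage |
|---|---|---|---|---|---|
| 14, 6 | 3, 2.5 | 15% | 10.28 | 9.18 / 8.12 | 11% / 21% |
| 14, 6 | 3, 2.5 | 50% | 10.28 | 9.64 / 9.03 | 6% / 12% |
| 14, 4 | 3, 2.5 | 15% | 10.44 | 9.94 / 9.44 | 5% / 10% |
| 14, 4 | 6, 4 | 15% | 7.43 | 7.27 / 7.09 | 2% / 5% |
| 14, 4 | 6, 4 | 50% | 7.43 | 7.35 / 7.27 | 1% / 2% |

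With OR = 1 the shrinkage is zero in every row.

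**What drives the result.** Selection with log-odds slope b = −ln(OR) lowers a group's mean by roughly b(1 − u)σ². The contrast therefore falls by roughly b(1 − u)(σ²_high − σ²_low). In the first row the SDs after truncation are 5.45 and 2.07. With OR 0.95, b = 0.0513, and 0.0513 × 0.85 × (29.70 − 4.28) = 1.11. The direct calculation gives 10.28 − 9.18 = 1.10. Equal spread and equal selection almost cancel. A separate check on standardised normal scores agrees: with equal SDs, a 1 SD contrast changed by 0-4%.

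**The case against.** **The authors acknowledge selection at consent.** They do, and openly. What remains is that the check they attach to it is worded for missing data only. Because that sentence follows remarks on both non-consent and attrition, it could be read broadly. If that is the intention, a few added words would settle it.

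**A condensed article may leave participation weighting to an analysis plan.** This is fair, and silence alone would be no finding. Here the article goes further: it states a threat and pairs it with a response that, on its ordinary meaning, does not reach it.

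**A reader might infer that decliners and day-7 removals are replaced by the next invitee, so that each group fills with its better-off members.** The documents do not say this. Replacement is implied by equal recruitment in random invitation order, but no replacement rule is written. The bias does not depend on one either, since the starters are self-selected whether or not places are refilled.

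**A reader might also infer that trajectory contrasts will certainly shrink.** The article speaks only of possibility. Material shrinkage needs wider spread or stronger selection in the more severe groups. A low-symptom group near the floor of the scale may well have the narrower spread, but that is an expectation and not a figure in the documents.

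**The magnitude rests on assumed SDs.** This stands: moving from SDs of 6 and 2.5 to 4 and 4 takes most of the effect away. The illustration also uses the SMFQ as a stand-in for EMA depression level, which is measured with adapted PHQ items. It shows nothing about the within-person associations that are central to RQ2.

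**Conclusion.** The point holds in a limited form. Non-consent is acknowledged as a possible source of selection, and day-7 removal takes people out before EMA begins. The one stated sensitivity analysis does not cover either group. Those who start may be less unwell than the trajectory they represent, and between-trajectory contrasts in EMA depression level may be biased as a result.

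The size is unknown from the documents. Under the assumed inputs it runs from about 1-5% shrinkage (SD 4 in both groups) to about 6-21% (SD 6 versus 2.5), and is zero if joining does not depend on score. These ranges illustrate the mechanism and are not estimates for this study. It is still worth acting on, because eligibility guarantees that every invitee has the scores needed to measure the selection.

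**What to change.** 1. Keep everyone invited, including day-7 removals, as the denominator. Because invitation order is random, the invitees are a fair sample of the people in each trajectory who could be invited.
2. Report, by cohort and trajectory, the numbers and 2025 depression scores of starters, decliners and day-7 removals.
3. Beside the unweighted trajectory comparisons, add a sensitivity analysis with inverse-probability-of-participation weights. Estimate the weights within cohort and trajectory from data already held: 2025 score, earlier scores and sex.
4. Extend the sensitivity-analysis sentence in Limitations from missing data to non-participation and day-7 removal.

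The cost is wording, one participation model, and slightly wider confidence intervals in the weighted analysis. No new contact or data collection is needed, but the invitation, decline and removal records must be kept while recruitment runs. The weights correct only for selection on the measured variables; worsening since the 2025 questionnaire, for example, would not be captured.
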